### Statistical analysis

A patient flow-chart shows the number of patients eligible and the numbers enrolled at each site. No imputation is envisaged to be performed for next of kin where the primary outcome is unknown. Summary statistics will be presented for continuous variables, and counts and percentages presented for categorical variables.

All analyses will apply the intention to treat principle. For example in a case where the intervention was not properly followed, such as the SaNOK had organ donation raised by an inappropriate requester instead of a designated requester, the patient will still be included in the study and considered to have received the intervention.

Paediatric cases defined as those aged less than or equal to 16 years, will be analysed as a separate cohort.

#### To address the primary endpoint

Consent rates provided by the next of kin for organ and tissue donation where the potential donor had not registered their decision will be calculated.

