## Methods/Design

### Aims and hypothesis

The aim of this study is to examine the process of organ donation decision-making, and to test whether changes in requesting practices change rates of family consent for organ donation and other family-based outcomes. A secondary aim is to examine whether changes in requesting practices result in increased satisfaction by families with their donation decision. The hypothesis for the trial component is that, compared to current usual practice, a ‘best practice’ family approach intervention will increase the family consent rate for deceased organ donation.

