### Design

This is a pre-post intervention design where rates of consent for organ donation for at least six months before implementation of the program in each ICU will be compared to the rates of consent for organ donation under the intervention.

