### Endpoints

The primary endpoint for the study is the family consent rate for deceased organ donation where the potential donor had not previously registered their donation wishes.

Secondary endpoints are: health professionals’ adherence rates to core elements of the COMFORT intervention; identification of predictors of family donation decision; and the proportion of SaNOK who report they regretted their final donation decision at around 90 days after enrolment.

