#### Current control

To describe practice for the ‘control condition’ i.e. pre-intervention details of donation events for the period of six months before each site implements the intervention and joins the program will be extracted retrospectively. Data will include: eligibility for deceased organ donation; patients’ date of birth, donation intent registered on their motor vehicle licence and the Australian Organ Donor Register; initiator of the donation conversation; family final donation decision, and outcome of the donation event.

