### Statistical methods

The sample size calculation was performed using the Simon’s two-stage design [44]. 140 eligible next of kin families are required to be approached to provide consent for organ donation. This will yield 80% power with 95% confidence to exclude a consent rate of 29% in favour of a clinically worthwhile rate of 40% for the intervention. An eligible next of kin family are those of patients who had not registered their donation decision.

Additionally, in the first 46 eligible next of kin families who are approached, if less than 15 have consented to organ donation, consideration will be given to modifying the study.

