#### Additional analysis: consent rates over time

Consent rates for hospitals that have participated in the “best practice” family approach intervention training will be compared up to six months before the site initiation visit with the consent rates under the intervention.

To establish the baseline (pre COMFORT) and concurrent data trends NSW state-wide, consent rates in hospitals not participating in “best practice” family approach intervention training at any point during the study will be presented over time.

The consent rates between NSW hospitals that had ICU health professionals trained in the intervention and NSW hospitals that never received the training will be presented. This analysis will only include families that were approached about organ donation before the hospital introducing the intervention training.

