Practical issues related to the delivery of a multi-centre trial made a staged roll-out of implementation necessary. However, operational issues, including the turn-over of DSNs and the time required for the requisite numbers of designated requesters to complete all training workshops (up to a year), caused delay in recruitment at some sites. The original plan for sequential start in equally spaced time periods could not occur. Practical issues may also affect protocol adherence; for example, without funding to allocate designated requesters to on-call rosters, availability is dependent on usual rostering procedures. Implementation of the intervention is therefore pragmatic being dependent on factors that will equally affect any future delivery as part of routine practice as well as a research intervention.

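### The hypothesis compares the intervention with usual practice, but the sample size and primary analysis concern a single rate set against a fixed 29%; the pre-post contrast is only an additional analysis

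*Protocol article*

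**What the plan says.** Five parts of the protocol article bear on this.

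- **Aims and hypothesis.** Relative to current usual practice, the best-practice "family approach intervention will increase the family consent rate for deceased organ donation".
- **Design.** A pre-post study in which "rates of consent for organ donation for at least six months before implementation of the program in each ICU will be compared" with the rates under the intervention. The abstract says the same.
- **Statistical methods.** "The sample size calculation was performed using the Simon’s two-stage design". The requirement is 140 eligible families, 80% power and 95% confidence to exclude 29% in favour of 40%, with a look after 46 families. No control-period number is given. Background gives 29% as unpublished 2011 NSW data for families offered donation when the patient had not registered a decision.
- **To address the primary endpoint.** Consent rates "for organ and tissue donation where the potential donor had not registered their decision will be calculated". No comparator, interval or decision rule is named.
- **Additional analysis: consent rates over time.** Rates in participating hospitals "will be compared up to six months before the site initiation visit with the consent rates under the intervention". Consent in hospitals that never took part is also to be presented over time.

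The outcome wording also differs. Endpoints defines the "family consent rate for deceased organ donation where the potential donor had not previously registered their donation wishes", while the primary analysis counts organ and tissue donation.

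**The concern.** The contrast that would test the hypothesis is not the primary analysis, and the sample size was not built for it. The only inferential test with stated operating characteristics compares the intervention-period rate with a constant taken from 2011.

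A constant cannot move with time. Background reports rising consent in NSW over the years just before the study, and the Discussion concedes that national training may raise consent independently of the intervention. A rate above 29% would then be read as support for the hypothesis when it may only show that usual practice in NSW had improved. A reader may also take the 80% power to apply to the before-after comparison, which it does not.

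**Working it through.** **1. The plan's own figure.** Inputs from Statistical methods: first stage 46 families, with fewer than 15 consents prompting reconsideration (so 14 or fewer); total 140; rates 29% and 40%. The protocol gives no final cut-off; the calculation uses 50 or more consents of 140.

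P(success | p) = Σ over x = 15 to 46 of P(X₁ = x | 46, p) × P(X₂ ≥ 50 − x | 94, p)

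- p = 0.29: 0.042 (one-sided error)
- p = 0.40: 0.800 (power)

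The stated design reproduces as a single-arm test against a fixed 29%.

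**2. What secular change does to that test.** Background gives all-case NSW consent of 51% in 2011 and 62% in 2013: 62 − 51 = 11 points. The target is 40 − 29 = 11 points. The protocol does not give the trend in unregistered cases, so the drift below is an assumption. The same formula, with no intervention effect, gives:

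| Assumed usual-practice rate in unregistered cases | Chance of passing the rule |
|---|---|
| 29% (no drift) | 4% |
| 32% (3 points) | 16% |
| 34.5% (half of 11 points) | 35% |
| 40% (all 11 points) | 80% |

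**3. Power of the pre-post contrast.** Two proportions, 29% v 40%, two-sided 0.05, no clustering, 140 intervention families. The control number n_C is assumed, because the protocol gives none.

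Power = Φ[(0.11 − 1.96 × SE₀) / SE₁], where p̄ = (0.29n_C + 0.40 × 140)/(n_C + 140), SE₀ = √[p̄(1 − p̄)(1/n_C + 1/140)] and SE₁ = √[0.29 × 0.71/n_C + 0.40 × 0.60/140].

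- n_C = 40: SE₀ = 0.0868, SE₁ = 0.0828, power 23%
- n_C = 70: SE₀ = 0.0704, SE₁ = 0.0682, power 34%
- n_C = 140: SE₀ = 0.0568, SE₁ = 0.0564, power 49%
- n_C = 280: SE₀ = 0.0485, SE₁ = 0.0495, power 62%

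For 80% power at 1:1, with p̄ = 0.345: n = {[1.96√(2 × 0.345 × 0.655) + 0.8416√(0.2059 + 0.2400)]/0.11}² ≈ 292 families per period.

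**4. Clustering, if the single-arm test stays primary.** Nine hospitals (Settings): m = 140/9 = 15.6. The intracluster correlation (ICC) is assumed.

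Design effect = 1 + (m − 1) × ICC

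- ICC 0.02: 1 + 14.6 × 0.02 = 1.29
- ICC 0.05: 1 + 14.6 × 0.05 = 1.73

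Normal tail for a single look at 50 of 140 under 29%: mean 40.6, variance 140 × 0.29 × 0.71 = 28.8, z = (49.5 − 40.6)/√(28.8 × design effect). One-sided error is 0.049 without clustering, 0.072 at ICC 0.02 and 0.104 at ICC 0.05. These figures concern the single-arm test only.

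In simulations of an unadjusted pre-post contrast (about 45 control and 140 intervention families), two-sided error stayed at 0.045 to 0.050 when site effects were the same in both periods. It was about 0.07 at ICC 0.05 only when half the site variance was specific to a period.

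**The case against.** The article condenses a fuller protocol, and an unseen analysis plan could supply the comparison method. Read with the sample size, the primary analysis is coherent as a single-arm evaluation against 29%, and the pre-post contrast is at least listed. It is true that methods are commonly left to the analysis plan. That does not reconcile a comparative hypothesis and design with a single-arm sample size and a contrast labelled additional, because those statements are all in this document.

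The trend argument has a limit. The 51% to 62% rise covers all cases, and the trend in unregistered cases is not given.

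Stronger readings are tempting but unsupported:

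- **That the pre-post comparison is crude and treats families as independent.** The article names no method for it. Silence does not show that site is ignored.
- **That site mix distorts the comparison.** The Discussion says "The original plan for sequential start in equally spaced time periods could not occur", so site weights may differ between periods. But no site durations or site-specific rates are given, and the figure with the data collection periods is not in the text available. With equal control weights, intervention time falling from 24 to 3 months and baseline consent from 40% to 20% across nine ICUs, the spurious difference is +3.2 points. Reversing the order makes it −3.2. Milder assumptions (12 to 24 months, spreads of 10 to 30 points) give 0.7 to 2.1.
- **That the control extraction is inadequate.** It lists date of birth and "initiator of the donation conversation; family final donation decision, and outcome of the donation event", and the statewide notification data cover the donation-event variables.

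**Conclusion.** The point holds as a mismatch within the protocol: a comparative hypothesis and design, a single-arm sample size, a primary analysis that only calculates rates, and the relevant contrast placed outside it. The primary result as written cannot show improvement over usual practice.

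The size rests partly on assumptions. The all-case NSW rise equals the 11-point target, so secular change is a credible alternative explanation, though its extent in unregistered cases is unknown. The 80% power belongs to the test against 29%; for the contrast it is about 25 to 50% with an assumed 40 to 140 controls. If the single-arm test is kept, an assumed ICC of 0.02 to 0.05 gives a design effect of about 1.3 to 1.7.

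Site-mix bias is possible given the unequal starts, but neither its size nor its sign can be determined from the document. The organ versus organ-and-tissue wording is a smaller inconsistency that should be settled with the same edit.

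**What to change.** In the section on the primary endpoint, address the hypothesis with the within-ICU pre-post contrast in consent to organ donation among unregistered cases. Stratify by ICU (Mantel-Haenszel, or logistic regression with ICU terms), report the risk difference and odds ratio with 95% confidence intervals, and set the result against the concurrent trend in non-participating NSW hospitals, which is already collected.

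Donor age may be added as a covariate. Do not adjust for who initiated the conversation: the designated requester is part of the intervention, so adjustment would remove some of the effect being estimated.

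In Statistical methods, state that the 80% power applies only to the single-arm test against 29%, and give the contrast's lower power for the expected number of controls. The control window needs one definition, since the article variously gives at least six months, six months and up to six months.

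If the single-arm test is to remain primary, say so, allow for clustering by ICU in its interval, and limit the conclusion to consent exceeding 29%. In either case, make the primary analysis read organ donation, as in Endpoints.

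The cost is wording, a wider interval and a less favourable stated power for the comparison. The data needed are already planned for collection.

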#### To address the secondary endpoints

Adherence to core elements of the intervention will be obtained via the case report form and rates calculated.The proportion of all next of kin who report they regretted their final decision either to consent or to decline donation at 90 days will be calculated with 95% Confidence Interval.Characteristics of the donation process including staff adherence to core elements of the intervention and demographic characteristics of the potential donor, senior next of kin and of the requester will be explored. Exploratory analysis using both univariate and multivariate regression methods will be used as needed. A *p-*value of < 0.05 will be considered statistically significant for retention in the multivariate model and only univariate variables with a *p-*value <0.20 will be considered for inclusion to the multivariate model.

Categorical data (e.g. details of gender, religion, ethnicity of patient and health care professional and reasons to consent or decline donation) will be summarised by frequencies and percentages. Continuous data (e.g. age, time in family meetings) will be summarised using the mean and standard deviation.

#### Additional analysis: consent rates over time

Consent rates for hospitals that have participated in the “best practice” family approach intervention training will be compared up to six months before the site initiation visit with the consent rates under the intervention.

To establish the baseline (pre COMFORT) and concurrent data trends NSW state-wide, consent rates in hospitals not participating in “best practice” family approach intervention training at any point during the study will be presented over time.

The consent rates between NSW hospitals that had ICU health professionals trained in the intervention and NSW hospitals that never received the training will be presented. This analysis will only include families that were approached about organ donation before the hospital introducing the intervention training.

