### Specialised communication training

In Australia, training in specialised communication for health professionals who offer donation has been a key component of a national reform agenda [38]. A national program of specialised training in family-centred communication regarding organ donation, developed in collaboration with the Gift of Life Institute (Philadelphia, USA), was introduced in October 2011 [39]. The revised program delivered in two modules over three days, incorporated face-to-face presentations of theory followed by practical training with role-play exercises [40]. This approach — the Organ and Tissue Authority (OTA) Family Donation Conversation (FDC) core and practical modules – (see Additional file 1) has been adopted as ‘best practice’; intensive care specialists and organ donation health professionals elect to attend, and the College of Intensive Care Medicine made completion of the core module a mandatory training requirement for intensive care trainees from 2014 [41]. However, role-play alone may not adequately replicate the emotional nature of donation conversations.

In NSW, training for health professionals selected as “designated requesters” to lead donation conversations has been supplemented by a simulation program [4]. Piloted in 2012 the program uses real donation scenarios with standardised relatives played by professional actors [42]. Health professionals are able to rehearse, review and reflect on their developing effective communication skills when offering donation in a protected learning environment, and thereby become more comfortable discussing these topics. These ‘best practice’ methods involving use of specialised requesters to lead deceased organ donation discussions with families are based on work from other countries adapted to but not formally tested in Australian conditions. This study will examine implementation of a ‘best practice’ family approach intervention and identify its effectiveness in terms of family consent rates, and later decisional satisfaction or regret.

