#### Consent rates over time

To describe trends in family donation decisions over the same time period as the COMFORT study and identify any trends/changes over time notification data from all NSW hospitals ICUs and Emergency Departments are collected. Data variables collected have been listed at *Donation events*, above (with the addition of ethnicity, religion, ICU stay and retrieval data as appropriate).

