There are some limitations of this study. Firstly, there were constraints on design. A pre-post intervention design was chosen in order to maximise recruitment and obtain an adequate sample size within a reasonable time period. Alternative designs were not feasible. For example, a randomised controlled trial design would have incurred high likelihood of contamination of ‘control’ sites by features of ‘best practice’ once national education began to be delivered in NSW. Cluster randomised control designs were discounted due to insufficient numbers of hospitals in NSW. A stepped wedge design was not possible as the crossover point for each site was primarily dependent upon staff release for the designated requester training, which in turn was dependent on local staffing; consequently this could not be randomly allocated. The pre-post design enabled all units to participate in the intervention and made economical use of ‘control’ data from every site.

Secondly, there are some potential threats to the validity of study findings. The delivery of the national FDC training may result in increased family consent rates independent of the study intervention. However, this training is only one part of the support planned for core elements of this intervention, so, if effective, consent rates would still be expected to increase more rapidly under the ‘intervention’ compared to the ‘control’ condition. We are unable to gauge the impact of ongoing community education activities directed to increase the proportion of people who register their donation decision. Selection bias is acknowledged for the follow-up interviews, in that those families who either were not offered or do not wish to have bereavement aftercare are excluded from this portion of the study.

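### Consent data from all NSW hospitals are collected but only displayed, so no stated analysis formally controls the pre-post effect for secular change

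*Protocol article*

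**What the plan says.** Under Additional analysis: consent rates over time, the protocol article states three analyses.

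1. Within participating hospitals, consent before the site initiation visit is compared with consent under the intervention. No term for calendar time is mentioned.
2. For hospitals that never take part, consent is shown over time, to establish baseline and concurrent state-wide trends.
3. Trained and never-trained hospitals are set side by side, with this limit: "This analysis will only include families that were approached about organ donation before the hospital introducing the intervention training".

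The data for more than this are gathered. Under Consent rates over time, in the evaluation section, "notification data from all NSW hospitals ICUs and Emergency Departments are collected" for the same period as the study. The variables refer back to Donation events, which lists donation intent on a register and the family's decision. The primary-endpoint population (families of unregistered patients) can therefore be identified in non-participating hospitals too.

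The Discussion concedes that national training may raise consent independently of the study. It answers that "consent rates would still be expected to increase more rapidly under the" intervention than under the control condition.

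**The concern.** Secular change is the main threat to an uncontrolled pre-post comparison, because anything else that raises consent between the two periods is counted as intervention effect. The article recognises this, and its answer is a claim about relative rates of rise. Testing that claim needs the change in participating hospitals to be compared with the change over the same months elsewhere. None of the three analyses does so: the first has no concurrent comparator, the second is a display, and the third contains no intervention-period families. A positive pre-post result would therefore carry no estimate of how much of it is trend, although the data that could supply one are being collected.

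**Working it through.** **Step 1. The plan's own target.** "The sample size calculation was performed using the Simon’s two-stage design", and the sample is meant to satisfy this: "This will yield 80% power with 95% confidence to exclude a consent rate of 29% in favour of a clinically worthwhile rate of 40" per cent. The target effect is 40 − 29 = 11 points. The stage-one rule is given as "in the first 46 eligible next of kin families who are approached, if less than 15 have consented to organ donation". With 46 families at stage one, 140 in total and success at c or more consents, treating the stage-one rule as a stop:

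P(success | p) = Σ (x = 15 to 46) P(X₁ = x) × P(X₂ ≥ c − x), with X₁ ~ Bin(46, p) and X₂ ~ Bin(94, p).

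The article does not print c. A search gives c = 50, with one-sided alpha 0.0416 at p = 0.29 and power 0.8002 at p = 0.40. The stated 140 therefore reproduces. The calculation sets one group against a fixed rate, so the sizing makes no allowance for trend either.

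**Step 2. What each stated analysis can show.**

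| Analysis | Participating hospitals, intervention period | Concurrent comparator | Formal contrast |
|---|---|---|---|
| Pre-post within participating hospitals | yes | no | yes |
| Non-participating hospitals over time | no | yes | no |
| Trained vs never-trained | no | pre-training only | between groups, baseline only |

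No row has all three. The third row also lacks a cut-off for never-trained hospitals: the limit is tied to a hospital introducing the training, which they never do.

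**Step 3. Possible size of the trend.** The inputs, from the Background, are overall annual consent rates for 2011 and 2013.

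- NSW: (62 − 51) / 2 = 5.5 points a year.
- National: (61 − 57) / 2 = 2 points a year.

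The article gives no length for the intervention period. Assume a six-month control period followed directly by D months of intervention. The gap between midpoints is 3 + D/2 months, which is 9 months for D = 12 and 15 months for D = 24.

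| Annual rate assumed to carry over | 9 months (× 0.75) | 15 months (× 1.25) |
|---|---|---|
| 2 points | 1.5 points | 2.5 points |
| 5.5 points | 4.1 points | 6.9 points |

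Against the 11-point target the range runs from 1.5/11 = 14% to 6.9/11 = 63%.

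**Step 4. Precision of a controlled estimate.** For illustration, take 140 intervention families at 40%, and the other three cells (participating before, comparators before and after) at 29% with m families each. The article gives no m. Treating families as independent:

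SE = √(0.40 × 0.60/140 + 3 × 0.29 × 0.71/m); power = Φ(0.11/SE − 1.96).

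| m | SE | 95% half-width (1.96 × SE) | Power for 11 points |
|---|---|---|---|
| 70 | 0.103 | 20 points | 19% |
| 140 | 0.078 | 15 points | 29% |
| 280 | 0.063 | 12 points | 42% |

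Clustering by hospital is ignored here.

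**The case against.** The best defence is that the article handles secular change openly. It names the threat, explains why randomised, cluster-randomised and stepped-wedge designs were not feasible, and shows concurrent trends in non-participating hospitals. Time terms, model form and clustering are commonly left to a statistical analysis plan, which is not shown. This defence stands in part. The missing model detail is not the point. The point is that the article does list its between-hospital analyses, confines the only contrast to the pre-training period, and then rests its answer to the threat on a contrast it does not list.

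Four stronger readings are tempting, and the document does not support them.

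- *Nothing separates the intervention from the trend.* The display of non-participating hospitals can be read informally beside the pre-post change. The gap is in formal control.
- *An 11-point background rise could explain the whole 11-point target.* The rise from 51% to 62% is the overall NSW rate, including registered patients. It covers 2011 to 2013, and the trial was registered in mid-2013, so much of the rise probably precedes the intervention. The national rise over the same years was 4 points.
- *The never-trained group shrinks because training became compulsory.* The article says that "the College of Intensive Care Medicine made completion of the core module a mandatory training requirement for intensive care trainees from 2014". That is one module for trainees. Designated requesters also need the practical module and the simulation workshop, so the mandate does not by itself move a hospital out of the never-trained group.
- *The pre-training restriction is itself the error.* It is the right restriction for a baseline comparability check.

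It is also fair to object to a controlled estimate as the main result. There are nine treated hospitals, the roll-out followed staff release and not chance, and the power in step 4 is low. That objection stands, and it sets the role of the remedy.

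**Conclusion.** The point holds in this form: concurrent state-wide data are collected but only displayed, and no stated analysis formally controls the pre-post effect for secular change. The argument in the Discussion about a faster rise is therefore left untested. The possible bias is roughly 1.5 to 7 points against an 11-point target. That range rests on two assumptions that the article cannot confirm: that overall 2011 to 2013 trends carry over to unregistered families during the study, and that the period midpoints lie 9 to 15 months apart. It shows that the bias could matter and is not an estimate of it. That the contrast is absent follows from the text alone and needs neither assumption.

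**What to change.** Under Additional analysis: consent rates over time:

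- Add a prespecified supportive controlled before-after estimate with its confidence interval, in families of unregistered patients across all NSW hospitals. Include hospital effects, a parsimonious calendar-time term and an intervention indicator that switches on at site initiation. Allow for clustering by hospital with a small-cluster correction.
- Define comparators as hospitals with no COMFORT site initiation, which avoids any doubt over what counts as training.
- Report this estimate beside the crude pre-post comparison.
- Keep the pre-training-only table, label it a baseline comparability check, and state a calendar cut-off for the never-trained hospitals.

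The cost is analysis work on data already being collected. The interval will be wide: half-widths of about 12 to 20 points under the cell sizes assumed above, before clustering. Parallel trends must be assumed, which a non-random roll-out makes less secure. Spill-over of national training to comparator hospitals may make the estimate conservative.
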